### Recruitment

Participants will be purposefully recruited through a systematic process. Trained FCHVs will identify potential participants who meet the CIDT criteria, such as individuals whose personal experiences align significantly with the CIDT story, exhibit impaired daily functioning, and express a need for support. Once identified, FCHVs will provide the details (age, gender, location) of individuals who meet CIDT criteria to their supervisor via a phone call. The supervisors will assess the eligibility criteria (i.e. 18 years or older, ability to speak, and CIDT threshold) and send the case details to the first author ([name]) for randomization.

Bi-monthly group meetings will be held for FCHVs to share their progress, discuss challenges encountered during the implementation of the CIDT, and provide motivation. Supervisors will also conduct field visits to offer immediate feedback and enhance FCHVs’ skills in utilizing the CIDT to ensure an effective recruitment strategy.

### Sample sizes and sampling process

The sample size for this study was determined based on the need to detect a difference in help-seeking behaviour between participants receiving the mental health literacy component (i.e. information about depression) alone (40%) and those receiving both the mental health literacy and stigma, myths, and facts about depression components (60%) [32, 53]. With 90% power and a significance level of 0.05, a total sample size of 288 participants is required, with 36 participants per condition. This sample size will allow to determine which component of the Gain-Life intervention positively impacts the primary outcome of help-seeking behaviour among individuals with depression.

### Randomization

Participants will be randomly assigned to one of eight treatment conditions based on four factors: (i) information on depression, (ii) available treatments, (iii) stigma reduction through myths and facts, and (iv) life transformation experiences. Using Microsoft® Excel (Version 16.86), a list of random numbers between one and eight with no duplicates was generated for each FCHV. As the FCHVs enrol participants, the first author assigns the next random number on their list to each participant, indicating the allocated treatment condition. Because each FCHV will recruit between 8 and 10 participants and there are only 8 treatment conditions, some FCHVs ended up delivering each condition at least once, and some conditions will be delivered twice. The table below summarizes the allocation of participants into different intervention components.

The first author will randomize each case using a computer-generated random table and assign them to one of the eight factors presented in Table 1 below. The randomization will be conducted separately for each FCHV to ensure cases are allocated to all 8 factors. The first author will inform the supervisors of the randomization results within 24 h. The supervisors will then inform FCHV which intervention or combination of interventions should be delivered to each case via a phone call.

**Table 1 Tab1:** Random allocation of participants into different intervention components

Experimental condition/factors	Information about depression	Information about available services	Stigma reduction	Recovery story (video)	Sample size
1	**✓**	**✓**	**✓**	**✓**	36
2	**✓**	**✓**	**✓**		36
3	**✓**	**✓**		**✓**	36
4	**✓**	**✓**			36
5	**✓**		**✓**	**✓**	36
6	**✓**		**✓**		36
7	**✓**			**✓**	36
8	**✓**				36

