### Blinding

Data collectors conducting baseline and follow-up interviews will remain blinded. The Principal Investigator (PI), trainers/supervisors, FCHVs, and participants will not be blinded to the treatment conditions. The PI, who is responsible for managing the study, randomizing participants, and supervising field activities including quality control, will not be blinded to the treatment condition. The statistician, who analyzes the quantitative data for the study, remains blinded (Fig. 1).

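### As described, allocation is not concealed from the person who assigns it: the list holder is sent case details before reading off the next number

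*Protocol article*

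**What the plan says.** The protocol article sets out the whole chain from detection to allocation.

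- **Recruitment.** "FCHVs will provide the details (age, gender, location) of individuals who meet CIDT criteria to their supervisor via a phone call". The supervisor checks eligibility and is then to "send the case details to the first author" for randomization. The three items are named for the call to the supervisor; what is forwarded to the first author is not itemised.
- **Randomization, first paragraph.** "a list of random numbers between one and eight with no duplicates was generated for each FCHV", using Excel. As cases come in, "the first author assigns the next random number on their list to each participant, indicating the allocated treatment condition".
- **Randomization, second paragraph.** "The first author will randomize each case using a computer-generated random table". "The first author will inform the supervisors of the randomization results within 24 h".
- **Blinding.** "The PI, who is responsible for managing the study, randomizing participants, and supervising field activities including quality control, will not be blinded".

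No step is described that hides the next number from the allocator until the case is irrevocably registered. The Discussion names single-blinding as a limitation but does not mention concealment.

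**The concern.** Concealment means that whoever decides which person takes the next place cannot know what that place holds. Here one person appears to have the sequence, information about the case, time before replying, and a field-supervision role. The details are not needed to read the next number from a list. If two cases from the same FCHV are waiting, the order in which they are taken decides who gets which condition.

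Location, age and gender could plausibly be related to whether someone reaches a health care provider within a month. The article does not establish this. It does make distance to providers part of the services component, and it lists age and gender among possible moderators. A bias introduced at this step would stay in the intention-to-treat analysis, because participants are analysed as allocated.

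**Working it through.** **1. Which links are stated and which are inferred**

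| Link | Status |
|---|---|
| Lists of 1 to 8 without repeats, generated beforehand for each FCHV | Stated |
| First author gives the next number on the list | Stated |
| Case details reach the first author before the number is given | Stated |
| Up to 24 hours to return the result | Stated |
| PI randomizes, supervises the field and is unblinded | Stated |
| First author is the PI | Inferred: each is separately said to randomize |
| The list holder can see upcoming numbers | Inferred: someone reading from a pre-generated list has access to it, and no masking is described |
| Case details include age, gender and location | Probable: these are the details named one sentence earlier |

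**2. The plan's own figure.** The point does not depend on the sample size, but the scale below does. For 40% versus 60%, two-sided 0.05 and 90% power, the continuity-corrected formula gives 140 per level, 280 in total, within 3% of the stated 288. With 8 conditions of 36, each component compares 4 × 36 = 144 with 144.

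**3. What exchanging two pending cases does.** A list holds each condition once, so exchanging two cases within it always changes both conditions. For one component, 4 of the 8 conditions are on and 4 are off. Given the first case's status, 4 of the remaining 7 positions have the opposite status, so the component differs within the pair with probability 4/7 = 57%.

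**4. Possible size of the bias.** Two quantities are assumed, not taken from the documents: a 20-point difference in help-seeking probability within each pair, and a share s of participants affected, always steered in the same direction.

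- *s counts participants in pairs that differ on the component.* There are 288 × s / 2 = 144s pairs. Each adds 20/144 points to the on-minus-off difference. Bias = 144s × 20/144 = 20 × s points.
- *s counts participants in all steered pairs.* Only 4/7 of the pairs matter for a given component. Bias = 20 × 4/7 × s points.

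The standard error of a difference between 144 and 144 near 50% is √(0.25 × 2/144) = 0.0589. The rejection rate when the component has no effect, at two-sided 0.05, is Φ(−1.96 + b/0.0589) + Φ(−1.96 − b/0.0589), with b the bias as a proportion.

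| s | Bias, 20 × s | Rejection | Bias, 20 × 4/7 × s | Rejection |
|---|---|---|---|---|
| 5% | 1.0 point | 5.3% | 0.6 point | 5.1% |
| 10% | 2.0 points | 6.3% | 1.1 points | 5.4% |
| 20% | 4.0 points | 10.4% | 2.3 points | 6.7% |

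If s counted only participants in differing pairs whose order was actually reversed, the formula would be 40 × s. About half of such pairs fall in the wanted order by chance, so this is the first column's bias expressed on half the share.

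**5. Would the baseline comparison show it?** Steering on a two-level trait such as gender unbalances that trait by s (first definition) or 4/7 × s (second). At s = 20% this is 20 or 11.4 points, which is 3.4 or 1.9 standard errors of 0.0589. At s = 5% it is 5 or 2.9 points, below one standard error.

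**The case against.** The strongest reply is that the article already contains much of the protection. Eligibility is settled by the supervisor before the request, and numbers must be taken in order, so exchanging two pending cases would breach the stated procedure. Logging detail commonly sits in the full protocol, and the recruitment process map is not shown. Age and residence are also eligibility criteria, so forwarding them could serve an ordinary second check or case matching. With 8 to 10 cases per FCHV and a 24-hour window, overlaps within one FCHV should be uncommon unless recruitment is short or clustered.

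Most of this stands and limits the point. It does not remove it: the article itself describes a route that brings case information to the list holder, and the only check on the order rule is the person bound by it.

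A reader might infer more than the text supports:

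- **That the PI certainly receives age, gender and location.** These items are named only for the call to the supervisor.
- **That the list holder can query or turn back cases.** The first author is given no eligibility role and no stated power to return a case.
- **That steering would be invisible.** The planned baseline comparison covers age and sex and could reveal heavy steering on them. Location is not among its examples, and light steering would probably pass unnoticed.
- **That the Moderators section shows age and gender to predict help-seeking.** It lists them as moderators, and its rationale concerns rates of depression and anxiety, not help-seeking. Location is not listed.
- **That allocation was manipulated.** Nothing in the document suggests it.

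**Conclusion.** The point holds as a weakness in the described procedure: allocation is not concealed from the person who assigns it, and the opening is two cases from one FCHV pending at once. It rests on two well-founded inferences (first author is PI; list holder can see the list) and one probable reading (what the case details contain).

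The size cannot be derived from the documents. The range of about 0.6 to 1 point at 5% affected and 2.3 to 4 points at 20% depends on the definition of the share and on an assumed 20-point gap. That gap is as large as the whole design effect of 40% to 60%, and nothing in the article supports one of that size by age, gender or location. If steering is rare, the effect on the primary analysis is small. The case for acting is that the remedy costs very little, not that harm has been shown.

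**What to change.** In the Recruitment and Randomization sections, state that:

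1. after the eligibility check and before requesting allocation, the supervisor logs the case with a time stamp and a running number per FCHV, for example in the existing ODK system;
2. the request to the list holder carries only the FCHV code and the running number;
3. numbers are released strictly in logged order.

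The Timeline section puts the start of implementation in June and of baseline data collection in July 2024, so allocation had probably begun. For cases already allocated, audit the assignment order against the original Excel lists, report any departures, and add the lack of concealment to the limitations.

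The cost is wording in two sections, a few logged fields and minor supervisor time, with no extra participants or visits. The FCHV code may still indicate locality, so the risk is reduced but not removed while the PI holds the lists. Passing them to someone independent of recruitment and field supervision would go further, if such a person is available.

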### Blinding

Data collectors conducting baseline and follow-up interviews will remain blinded. The Principal Investigator (PI), trainers/supervisors, FCHVs, and participants will not be blinded to the treatment conditions. The PI, who is responsible for managing the study, randomizing participants, and supervising field activities including quality control, will not be blinded to the treatment condition. The statistician, who analyzes the quantitative data for the study, remains blinded (Fig. 1).

**Fig. 1 Fig1:**
[figure not shown]
Recruitment process map

#### Assessing and addressing harms

While this study carries a low risk, discussing mental health issues may be distressing for some participants. To mitigate these risks, we will provide access to trained counselors who can effectively handle such situations and make referrals to health care facilities if needed. Participants who report self-harm or suicidal thoughts will be promptly referred to counselors for immediate support.

### Description of the intervention

Previous studies have shown that mental health literacy is associated with help-seeking behaviour, suggesting that improved mental health literacy can increase the likelihood of seeking help [29, 72]. Similarly, several studies have found that higher levels of stigma, particularly related to seeking help for mental health issues and personal stigma, are significantly linked to reduced active help-seeking behaviour [21, 68]. A formative study identified lack of information about available services, lack of knowledge about mental health problems, and lack of support from family members as major barriers to seek care for mental health issues. Therefore, the Gain Life intervention was developed based on the evidence from previous studies and the formative study results. The intervention comprises four components: mental health literacy, stigma reduction, information on available services, and a video featuring a service user’s recovery story. Workshops were conducted with psychologists, psychosocial counsellors, and individuals implementing mental health interventions in the community to develop and finalize the contents for these components. The draft intervention was pilot tested with ten FCHVs in a different district to gather their feedback on the content, delivery mechanism, training duration and methods, and supervision needs.

#### Information about depression

The aim of this component is to raise awareness about depression, with a particular focus on its causes, manifestations, and the potential negative consequences of untreated depression. Previous studies have indicated that the causes of depression are often linked to stressful life events, socio-cultural factors, and genetic predispositions, rather than solely biological factors. In this component, we have highlighted various contextual factors, including cultural practices and beliefs, stressful life events such as natural disasters (e.g. earthquakes, landslides), economic hardships, changes in family structures, family stress, educational stress, genetic influences, social discrimination and exclusion, substance abuse, and chronic illnesses like cancer and HIV/AIDS.

In addition to the common symptoms of depression outlined in standard guidelines, we have included culturally and context-specific symptoms frequently reported by individuals with depression in Nepal, such as stomach-ache, headaches, unexplained body pains, and tingling sensations. Research has shown that individuals are more likely to seek care for their illness if they understand the negative consequences of leaving it untreated. Therefore, we have included information on the potential consequences of untreated depression, which can range from difficulties in daily activities and increased chronicity of the illness to reduced treatment effectiveness and higher treatment costs. This component is designed as a flipchart with animated images to engage participants. FCHVs can use the flipchart on a table or in a planned space, turning the pages to display images on participants’ side and the page containing the content on their side.

#### Information about available services

The second component of the intervention provides detailed information about mental health services available in the community, district, and neighbouring districts. This includes the types of services offered, costs, distance to service providers, and operating hours. Lack of knowledge about available services has been identified as a barrier to seeking mental health care. Studies have shown that patients often do not know where to seek help and may resort to traditional healers or avoid seeking care altogether. However, mental health services are now accessible in primary and community health care facilities through a task-sharing approach. The aim of this intervention component is to address the lack of awareness about available services and assist individuals in identifying suitable sources of support. It encompasses all treatment options, including primary health care providers who are on the mental health Gap Action Program (mhGAP) intervention guide and municipal hospitals, as well as specialist services within the district and neighbouring districts. This component is being produced as a booklet with images of specific health facilities and their surroundings on one side, and descriptions of available services and services that are not available on the other side. This format helps FCHVs associate the images with available services while implementing the component.

#### Stigma, myths and facts about depression

The purpose of this component is to address stigma and misconceptions surrounding depression by addressing the root causes of stigma, dispelling myths, and providing accurate information about depression. The component covers the stigma surrounding mental health issues, common stigmatized behaviours experienced by individuals with depression, and how stigma and discrimination can hinder help-seeking behaviour. The second part of the component focuses on debunking prevalent myths about depression and presenting the facts. This information is presented in a table format, with one column listing myths and another column providing factual information. The component is designed as a wall calendar with animated images to enhance understanding, particularly for participants with reading difficulties. FCHVs can use the calendar to display information on a wall or facilitate discussions by connecting the text with corresponding images.

### Training

#### Training to FCHVs

FCHVs will receive a 5-day training that includes the Community Informant Detection Tool (CIDT) and the Gain Life intervention. The first part of the training will cover basic concepts of mental health, reasons for underutilization of mental health services, and the CIDT’s purpose of identifying individuals with depression. FCHVs will learn to use vignettes for detection, recognize symptoms, and assess the need for depression support. Role-playing exercises will emphasize seeking help and involving family members.

The second part of the training will focus on the Gain Life intervention, covering theoretical and practical aspects. FCHVs will learn about mental health problems, depression, causes, symptoms, consequences of untreated depression, available mental health services, stigma associated with mental health problems, and strategies to reduce stigma. Role-playing activities in small groups will help FCHVs gain confidence in implementing the intervention effectively.

#### Training to primary health care providers

Primary health care workers in Kanepokhari and Pathari-sanischare municipalities have not received training on mental health. Therefore, they will undergo a 5-day mhGAP training based on the module developed by the government of Nepal. The training will focus on the assessment, diagnosis, and management of mental health conditions such as depression, psychosis, alcohol use disorder, epilepsy, anxiety, and child and adolescent mental and behavioural problems. The training will be conducted by a psychiatrist and a psychologist. Female Community Health Volunteers (FCHVs) who receive training in the Gain Life intervention will provide information on the services available in the health facilities where health workers are trained on mhGAP.

### Implementation process of Gain Life intervention

FCHVs will utilize the CIDT in their daily tasks to identify individuals experiencing depression. They will initially consider individuals whose experiences resonate with the CIDT vignette. Upon identifying a potential candidate, FCHVs will engage in a consultation to evaluate the impact of the issue on the individual’s daily life and their readiness to seek assistance. If the individual agrees to participate in the Gain Life intervention, FCHVs will arrange a suitable date and time for its implementation.

As per the study protocol, participants may receive all four components of the Gain Life intervention or a combination of three, two, or one component. FCHVs will coordinate the intervention implementation accordingly, with a maximum of two components being delivered simultaneously. In cases where three components are required, they will be administered on separate days. The intervention sessions will take place in confidential settings, such as the participant’s or FCHV’s residence, to ensure privacy. While family members are encouraged to join, participants who prefer not to involve them can opt for individual sessions.

Participants may choose not to receive all allocated components of the intervention for reasons such as feeling that they do not need the additional components, starting treatment after receiving initial components, or other contextual factors. These participants will still be included in the analysis using an intention-to-treat approach. Additionally, there will be no restrictions on participants receiving other interventions, support, or attending awareness programmes. These aspects will be explored in the qualitative component of the intervention.

### Supervision of FCHVs

Trained FCHVs will receive regular supervision from psychosocial counsellors in three ways. Firstly, they will participate in group supervision sessions twice a month to discuss challenges encountered while implementing CIDT and Gain Life interventions. The psychosocial counsellor will offer practical guidance and skills to address these challenges. Group supervision sessions will be held separately for FCHVs in Kanepokhari Rural Municipality and Patharisanischare Municipality. Secondly, each FCHV will undergo two live supervisions per month, during which the counselor will observe a Gain Life session. These sessions will only be observed if the participant or their family member feels comfortable. Lastly, the psychosocial counsellors will contact each FCHV before implementing the intervention to ensure they are using the correct components as allocated randomly.

